## Abstract

Insomnia is a common health problem that can lead to various diseases and negatively impact quality of life. Pharmacopuncture is a new type of acupuncture that involves applying herbal medicine extracts to acupoints. Korean medicine doctors frequently use it to treat insomnia disorder. However, there is insufficient evidence to support the effectiveness and safety of pharmacopuncture for insomnia disorder. We designed a pragmatic randomized controlled trial to compare the effectiveness of pharmacopuncture and acupuncture for insomnia disorder. This multi-site, randomized, acupuncture-controlled trial will enroll 138 insomnia patients. The subjects will be randomly assigned to one of two groups, pharmacopuncture or acupuncture, at a 2:1 ratio. For 4 weeks, the participants will receive ten sessions of pharmacopuncture or acupuncture treatment and will be followed up for 4 weeks after the treatment ends. The Pittsburgh Sleep Quality Index score is the primary outcome measure. Insomnia severity index score, sleep parameters recorded using actigraphy and sleep diaries, physical symptoms associated with insomnia, emotions, quality of life, medical costs, and safety are the secondary outcome measures. The findings of this trial willprovide evidence that will be useful in clinical decision-making for insomnia treatment strategies.

## 1. Introduction

Insomnia disorder is defined according to the Diagnostic and Statistical Manual of Mental Disorders, fifth edition (DSM-5) diagnostic criteria as difficulty falling asleep, maintaining sleep, or waking up too early in the morning despite adequate sleep opportunities, resulting in impaired daytime function [1]. Insomnia disorder is highly prevalent; various studies conducted worldwide have revealed that insomnia affects 10–30% of the population, with some estimates as high as 50–60% [2,3,4,5]. According to an epidemiologic study conducted in South Korea, approximately 20% of adults have insomnia [6]. Insomnia is linked to reduced productivity, poor job, or academic performance, an increased risk of workplace or traffic accidents, and an increased vulnerability to a variety of medical conditions such as psychiatric disorders, cognitive impairment, cardiovascular diseases, and metabolic diseases [7,8,9,10,11]. As a result, insomnia can negatively impact one’s quality of life as well as be a significant financial burden [12,13].

Socioeconomic status (SES)—defined by income, education, and employment—influences health disparities and social inequities and can affect public health outcome by different processes [14]. Recently, several studies reported that sleep health and sleep disturbance are correlated to SES. Poor income, low education, unemployment, and difficult living conditions are reportedly associated with poor sleep quality, insomnia, and excessive daytime sleepiness [15,16]. Moreover, a meta-analysis showed that the influence of SES on sleep health can be measured objectively and quantitatively through actigraphy or polysomnography [17].

In Western medicine, pharmacological treatment and cognitive behavioral therapy (CBT) are used to treat insomnia [18,19,20]. Pharmacotherapy, in particular, benzodiazepines are effective for the short-term (3–4 weeks) treatment of insomnia [20]. However, clinical guidelines state that short-term hypnotics administration should be supplemented with behavior and cognitive therapies when possible [4]. Moreover, long-term use of benzodiazepine increases the risk of abuse, tolerance, dependence, and associated medical complications such as falls, fractures, and impaired attention, psychomotor function, and cognitive function especially in older adults [21,22,23,24]. Meanwhile, CBT for insomnia (CBT-I) is recommended as the initial treatment modality for patients with chronic insomnia, with sleeping pills considered an adjunct to CBT-I [18,19]. CBT-I is not only effective in improving insomnia [25,26] but also comorbid insomnia with sleep apnea, arthritis, and coronary artery disorder [27,28]. However, some patients fail to achieve any benefit from this treatment [29], and there are some challenges in implementing CBT-I, including the lack of trained therapists, low patient motivation, and high burden of cost and time [29]. Recently, Internet-based CBT-I is shown to be as effective as in-person practitioner-administered CBT-I, and there are debates on the extent of therapist’s involvement in this treatment [30].

Acupuncture is the most frequently used treatment approach for insomnia in Korean medicine, as reported by a 2016 survey [31] and is reimbursed by the National Health Insurance (NHI) [32]. A systematic review including 15 randomized controlled trials (RCTs) with 1108 patients reported that acupuncture was more effective than sham or placebo acupuncture in improving subjective sleep quality, insomnia severity, and various sleep components [33]. The Clinical Practice Guideline of Korean Medicine for Insomnia Disorder states that acupuncture, as monotherapy and in combination with sleeping pills, should be considered in treating insomnia. The Clinical Practice Guideline of Korean Medicine for Insomnia Disorder was the first of its kind in South Korea to recommend traditional Korean medical interventions for treating insomnia. However, it was limited in that it did not recommend CBT-I as an initial treatment [34].

Pharmacopuncture is a new type of acupuncture therapy that involves injecting herbal medicine extracts into acupoints, thus producing a combination of mechanical and chemical effects. Its benefits include a relatively quick effect and ease of administered dosage control. Additionally, since the herbal medicine is administered and absorbed directly into the acupoints without direct involvement of the gastrointestinal tract, this treatment can be extended to patients who cannot consume herbal medicine orally [35]. Pharmacopuncture is frequently used for the treatment of insomnia, and more than one-third of Korean medicine doctors reported using this treatment for insomnia in 2016 [31]. A 2020 survey showed that the most commonly used type of pharmacopuncture for insomnia is placental pharmacopuncture, followed by Hwangryunhaedok-tang, Ouhyul, and Bufonis venenum pharmacopuncture [36]. A systematic review reported that the decrease in PSQI score after pharmacopuncture therapy was significantly greater than that after pharmacotherapy or acupuncture [37]. Korean medicine doctors theorize that pharmacopuncture may effectively and safely treat insomnia. However, the implementation of this therapy is limited in clinical settings because of insufficient clinical evidence and the high cost of procedure, which is due its exclusion from national health insurance coverage [36].

However, RCTs comparing the effectiveness and safety of pharmacopuncture and acupuncture on insomnia disorder are scarce. Furthermore, to the best of our knowledge, there have been no RCTs conducted in Korea comparing the effectiveness and safety of pharmacopuncture and acupuncture on the improvement of insomnia. 

Therefore, a well-designed RCT that can reflect the clinical status and context of Korean medicine is needed. We will perform a multi-site, pragmatic, randomized, acupuncture-controlled trial to investigate the effectiveness and safety of pharmacopuncture compared with acupuncture covered by NHI for insomnia disorder. The results of this study will provide clinical and economic evidence that will be helpful in clinical decision-making for various insomnia treatment strategies used in Korean medical clinical settings.

## 2. Materials and Methods

### 2.1. Study Design

This multi-site, pragmatic RCT was conducted at Pusan National University Korean Medicine Hospital, Dong-eui University Korean Medicine Hospital, and Semyung University Korean Medicine Hospital in Chungju. The study protocol was approved by each research institution’s institutional review board (IRB) before trial initiation (Pusan National University Korean Medicine Hospital, Institutional Review Board: PNUKHIRB-2021004; Semyung University Korean Medicine Hospital in Chungju, Institutional Review Board: SMCJH 2110-12; and Dong-eui University Korean Medicine Hospital, Institutional Review Board: DH-2021-13). The IRB will approve any changes to the study protocol, including recruitment advertisements, informed consent forms, and case report forms (CRF). The study protocol was registered with the Clinical Research Information Service (CRIS) (no. KCT0006803).

### 2.2. Participants Recruitment and Study Schedule

A total of 138 participants with insomnia will be recruited and registered for competitive enrollment. Potential participants will be recruited through internal advertisements on bulletin boards and the homepages of each clinical institution, external advertisements in local newspapers, subway advertisements, and flyer advertisements. The investigators, who are qualified neuropsychiatrists of Korean medicine, will explain the purpose, treatments, procedures of the clinical trial, and any risks and potential for adverse effects that may occur during this trial procedure. Participants will be asked to sign informed consent forms after investigators sufficiently explain this clinical trial, and receive a copy of the consent form. The investigators will then diagnose the insomnia disorder according to DSM-5 criteria. Eligible participants will be randomly assigned to the pharmacopuncture or acupuncture group in a 2:1 ratio at visit 1. They will visit the research institution 12 times and undergo 10 treatments 5 times every 2 weeks for 4 weeks (visits 1–10). Within 1 week of treatment completion, a post-intervention assessment will be conducted (visit 11), and a follow-up assessment (visit 12) will be performed 4 weeks after treatment completion. The timeline of enrollment, treatment, and evaluation of the participants is summarized in Table 1, and a flowchart of the trial is presented in Figure 1. Additionally, 15 consecutive participants from each group enrolled at the Pusan National University Korean Medicine Hospital after random randomly assignment will undergo polysomnography, melatonin, and cortisol saliva studies on the day before the initiation of treatment (visit 1) and at the post-intervention evaluation (visit 11).

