### 2.6. Randomization, Allocation Concealment, and Blinding

A statistical expert not involved in the assessment and intervention will generate the allocation sequence using a stratified block randomization method with the research institution as a stratification factor using the statistical program SAS 9.4 (SAS Institute, Cary, NC, USA). The randomization list will be delivered to each institution and stored in sealed opaque envelopes in a double-locked cabinet. The investigator will open the envelope to randomly assign the participants to the pharmacopuncture or acupuncture groups. The investigator will store the open envelopes in a double-locked cabinet and record the randomized number assigned to each patient on the electronic medical chart.

Due to the nature of the interventions, it will be impossible to achieve blinding of participants or health practitioners. Outcome measures will be assessed prior to treatment in separate rooms by assessors who are not involved in allocation and interventions to ensure assessor blinding. The assessors participating in this study are residents at the Department of Neuropsychiatry of Korean Medicine and clinical research coordinators who have completed research ethics education and standard operating procedure training related to this trial before trial initiation.

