## Figures and Tables

**Figure 1 ijerph-19-16688-f001:**
[figure not shown]
Flow diagram of the study.

**Table 1 ijerph-19-16688-t001:** Schedule of enrollment, intervention, and assessment.

Time Point	Screening	Enrollment Allocation (V1) Treatment: Total 10 Sessions (V1–10)				Post-Treatment Evaluation	Follow-Up
	Week −1	Week 0	Weeks 1–4			Week 5	Week 9
		V1	V2–5	V6	V7–10	V11	V12
Eligibility screening	O						
Informed consent	O						
Vital signs	O	O	O	O	O	O	O
Socioeconomic status, medical history	O						
ISI, HADS	O						
Laboratory tests and electrocardiogram	O					O	
Randomized allocation		O					
Pharmacopuncture (experimental)		← 5 times per 2 weeks →					
Acupuncture (control)		← 5 times per 2 weeks →					
ISI	O	O		O		O	O
PSQI		O		O		O	O
PIT for insomnia		O				O	
CSEI-S		O				O	
VAS of subjective symptoms accompanying insomnia		O		O		O	O
Quality of life (EQ-5D-5L, EQ-VAS, SF-36, HINT-8), Cost data		O				O	O
Body composition		O				O	
Request for additional treatment						O	
Sleep diary and actigraphy	O	O	O	O	O	O	O
Adverse event check		O	O	O	O	O	O
PSG, melatonin, cortisol *		O				O	

* PSG will be performed a day before visits 1 and 10. Melatonin and cortisol levels will be collected at 10 p.m. a day before visits 1 and 10 and at 7 a.m. on visits 1 and 10. Only 15 participants per group enrolled at Pusan National University Korean Medicine Hospital. ISI, Insomnia Severity Index; HADS, the Hospital Anxiety and Depression Scale; PSQI, Pittsburgh Sleep Quality Index; PIT for insomnia, Pattern Identification Tool Insomnia for insomnia; CSEI-S, The Core Seven-Emotions Inventory Short Form; VAS, visual analog scale; EQ-5D-5L, 5-level EuroQoL five-dimension questionnaire; EQ-VAS, the EuroQol-visual analogue scale; SF-36, the 36-Item Short Form Health Survey questionnaire; HINT-8, Korean Health-Related Quality of Life Instrument with 8 items; PSG, polysomnography.

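### Sub-study participants are to be picked by arm after an allocation made at visit 1, yet have polysomnography the day before visit 1; equal quotas under 2:1 also leave the two groups only partly concurrent

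*Protocol article*

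**What the plan says.** On allocation, section 2.2 states: "Eligible participants will be randomly assigned to the pharmacopuncture or acupuncture group in a 2:1 ratio at visit 1". The header of Table 1 agrees, placing allocation and the first treatment session at the same visit: "Enrollment Allocation (V1) Treatment: Total 10 Sessions (V1–10").

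On the sub-study, the same section 2.2 states: "15 consecutive participants from each group enrolled at the Pusan National University Korean Medicine Hospital after random randomly assignment will undergo polysomnography". The melatonin and cortisol saliva samples go with it, and the timing is "on the day before the initiation of treatment (visit 1) and at the post-intervention evaluation (visit 11"). The Table 1 footnote repeats the day-before timing for the baseline test: "PSG will be performed a day before visits 1 and 10". It sets the first saliva sample at 10 p.m. that evening and adds: "Only 15 participants per group enrolled at Pusan National University Korean Medicine Hospital".

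Section 2.6 describes a "stratified block randomization method with the research institution as a stratification factor" and says how an arm becomes known: "The investigator will open the envelope to randomly assign the participants to the pharmacopuncture or acupuncture groups". Participants and practitioners are not blinded. Outcomes are to be assessed before treatment; the section does not say before allocation.

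The primary outcome (section 2.9.1) is the change in self-reported PSQI from visit 1 to visit 11. In Table 1 the first PSQI is at visit 1; there is none at screening.

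**The concern.** A participant cannot be selected according to the arm drawn at visit 1 and also be tested on the evening before visit 1 because of that selection. Sites therefore have to depart from one of the two statements, and the article does not say which.

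One departure matters beyond the sub-study. If the envelope is opened a day or more early so that the right people can be booked, these open-label participants may know their arm when they sleep in the laboratory and when they complete the visit 1 PSQI. That score is one half of the primary outcome, and no earlier PSQI exists to check it against.

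The second issue is the pairing of equal quotas with 2:1 allocation. The larger arm fills its quota first, after which only acupuncture participants are wanted. That weakens the side-by-side comparison and adds a practical incentive to learn the allocation before visit 1.

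**Working it through.** The plan gives no derivation for 15 per group, so there is no figure to reproduce. The check sets the timings side by side and then works out how a 2:1 sequence fills two quotas of 15.

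**1. Order of events.** Inputs: section 2.2 and Table 1.

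- Arm known: visit 1.
- Selection: by arm, after the arm is known, so visit 1 at the earliest.
- Baseline polysomnography and 10 p.m. saliva: the day before visit 1.

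Selection must come before the test, but as written it comes after. Two departures are possible:

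- (a) The envelope is opened before visit 1. This contradicts section 2.2 and Table 1.
- (b) Participants are tested while unallocated. This contradicts selection after assignment. If testing continued until both quotas were full, about 44 baseline recordings would be needed (step 3) for 30 places, which also contradicts the limit of 15 per group.

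**2. Exposure under (a).** At most 2 × 15 = 30 participants; 30/138 = 22%. This counts sub-study places and is an upper limit.

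**3. When the quotas fill.** Without blocking, the expected number randomised at the site is 15/(2/3) = 22.5 for pharmacopuncture and 15/(1/3) = 45 for acupuncture. The plan uses blocks but gives no size, so 2:1 permuted blocks of 3, 6, 9 and 12 were assumed and simulated (10,000 sequences each):

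| Block size | Mean position of 15th pharmacopuncture | Mean position of 15th acupuncture | Mean acupuncture places filled after pharmacopuncture quota closes |
|---|---|---|---|
| 3 | 22.3 | 44.0 | 7.7 |
| 6 | 22.2 | 44.3 | 7.8 |
| 9 | 22.3 | 43.5 | 7.7 |
| 12 | 22.1 | 43.8 | 7.9 |

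Across block sizes the 95% ranges are 20–24 for the 15th pharmacopuncture participant, 40–47 for the 15th acupuncture participant, and 6–10 for the late acupuncture places. The acupuncture quota filled last in every run. About 7 of the 15 acupuncture participants are concurrent with pharmacopuncture sub-study enrolment and about 8 are not.

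**4. Can the site supply 15 acupuncture participants?** Enrolment is competitive with no number per site, so site size N is an assumption. The results are exact for each assumed block size.

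- N = 46 (138/3). Block 3: 15 full blocks give 15, so 100%. Block 9: 5 full blocks give 15, so 100%. Block 6: 7 full blocks give 14, and one more is needed in the next 4 places: 1 − 1/C(6,2) = 1 − 1/15 = 93%. Block 12: 3 full blocks give 12, and three more are needed in the next 10 places: 1 − C(4,2)/C(12,2) = 1 − 6/66 = 91%.
- N = 40. Blocks 3 and 6: at most 14, so 0%. Block 9: 12 plus all three in the next 4 places, C(4,3)/C(9,3) = 4/84 = 5%. Block 12: 12 plus at least three in the next 4 places, (4 × 8 + 1)/C(12,4) = 33/495 = 7%.
- N = 36. All four block sizes divide 36, giving exactly 12, so 0%.

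**5. Precision if 15:15 becomes about 20:10.**

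- Between-arm contrast: √(1/20 + 1/10) / √(1/15 + 1/15) = √(0.150/0.133) = 1.06.
- Acupuncture arm's own before-after change: √(15/10) = 1.22.
- Pharmacopuncture arm's own change: √(15/20) = 0.87, a gain.

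**The case against.** The best defence is that this is one visibly garbled sentence in a condensed article about a small exploratory sub-study. Section 2.9.5 frames it as exploration, the Discussion calls its output preliminary, and section 2.13 plans an analysis of changes before and after treatment rather than a clear between-arm test. Equal groups of 15 are a reasonable way to describe each arm, and polysomnography and hormone levels are less open to expectation than questionnaires. Table 1 also has the ISI, sleep diary and actigraphy at screening, so pre-allocation values of those exist for everyone.

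Most of that stands, and it limits the weight of the point. It does not remove the contradiction: both timings are stated outright, in the text and again in the table, so condensation does not explain them. Nor does it cover the PSQI, which has no screening value.

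Three stronger readings are tempting, and the documents do not support them:

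- *The primary baseline is compromised.* This follows only if the envelope is opened early. If testing is done on unallocated participants, no baseline is affected. Nothing in the article shows which happens.
- *The two sub-study groups are not concurrent.* They overlap over roughly the first 22 participants at the site. With a before-after analysis, non-concurrence weakens an arm comparison but does not undo the planned description.
- *Simple binomial odds of filling the acupuncture quota (60% at 46, 34% at 40).* Section 2.6 specifies blocks stratified by institution, which hold the count near one third. The blocked figures are the ones to use: better at 46, much worse at 40.

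**Conclusion.** The point holds as a contradiction that should be resolved. Allocation at visit 1 cannot be squared with selection by arm for a test the day before. The possible consequence for the main trial is that up to 30 of 138 participants (22%) know their arm before the primary-outcome baseline; this is conditional on early opening of envelopes, and neither its direction nor its size can be derived from the documents.

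The quota rule makes the sub-study groups partly concurrent, with about 8 of 15 acupuncture participants entering late. It also leaves feasibility sensitive to site size: near certain at one third of total enrolment, and very unlikely if the site falls six short of that. These figures rest on assumed block sizes of 3 to 12 and assumed site sizes, and on every eligible participant taking part. Because the sub-study is exploratory, the quota problem alone would be modest; protecting the baseline from knowledge of allocation is the main reason to act.

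**What to change.** Amend section 2.2 and the Table 1 footnote so that they agree, and state that:

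- baseline polysomnography, saliva sampling and all visit 1 baseline questionnaires are completed before the envelope is opened;
- sub-study participants are chosen without regard to arm, as 30 consecutive participants at that site, with the arms falling as randomised (about 20:10);
- for participants already enrolled, the record shows whether allocation preceded the baseline measures, so that a sensitivity analysis is possible.

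The same amendment should settle the second test, which section 2.2 and the Table 1 column place at visit 11 but the footnote places the day before visit 10.

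The number of paired recordings stays at 30 and the site needs only 30 participants, so the shortfall risk in acupuncture numbers no longer blocks completion. The price is about 6% more standard error for a between-arm contrast and about 22% more for the acupuncture arm's own before-after change. If equal description of both arms matters more to the sponsor, that loss is the trade-off to weigh; the requirement to finish baseline before opening the envelope costs almost nothing.

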### 2.3. Sample Size

In this trial, the ratio of the pharmacopuncture group to the acupuncture group will be 2:1 in order to obtain data on the side effects (safety) of the pharmacopuncture while securing statistical power [38,39]. The sample size of this study was determined based on the study by Xian et al. [40]. The mean differences in PSQI scores before and after treatment in the experimental and control groups were estimated to be 6.9 (standard deviation = 2.51) and 4.93 (standard deviation = 2.70), respectively. Based on this, the effect size calculated using G Power software, version 3.1.9.4 (Franz Faul, Christian-Albrechts-Universittt Kiel, Kiel, Germany) was 0.92. The number of participants required is then 74 for the experimental group and 37 for the control group, given a 2:1 allocation ratio, two-sided significance level of 0.05, and 95% statistical power. Considering a dropout rate of 20%, the total sample size of the experimental and control groups will be 92 and 46, respectively.

